### Interim analyses {21b}

Interim analyses are performed after the completion of the second measurement time point to evaluate step 1 of the STARKIDS intervention.

### Methods for additional analyses (e.g., subgroup analyses) {20b}

#### Qualitative interviews and focus groups

As an evaluation of the STARKIDS material, we conducted two focus groups and 9 interviews. The focus consisted of three parents of children with obesity and the children themselves. Materials from the STARKIDS program were shown and feedback was taken. The interviews were held at a later time point with five experts from a medical institution for children with obesity and four families being treated there. Materials (e.g., an educative movie, a serious game) were shown and feedback was taken.

#### Process evaluation

Participating pediatricians and medical assistants, as well as participating families are given questionnaires (tablet-based) to evaluate the STARKIDS program. The same items are given before and after the STARKIDS study as well as additional items about each participating family to assess their respective program fit. Items are rated on 5-point Likert scales.

### Methods in analysis to handle protocol non-adherence and any statistical methods to handle missing data {20c}

Protocol non-adherence will be accounted for through the use of covariates capturing pertinent aspects of such non-adherence in the regression models mentioned under the “Statistical methods for primary and secondary outcomes {20a}” section as well as separate analyses for observation groups with difference adherence levels. Potentially different results between these groups as well as a potential role of adherence as a predictor of treatment effectiveness will be transparently considered and accounted for.

Provided that missingness of data can be plausibly considered as missing at random, multiple imputation techniques will be used in order to avoid untoward loss of non-missing information that could occur through the use of other strategies (e.g., inadequate listwise deletion).

### Plans to give access to the full protocol, participant-level data and statistical code {31c}

The datasets analyzed during the current study and statistical code are available from the corresponding author on reasonable request, as is the full protocol.

### Oversight and monitoring

#### Composition of the coordinating center and trial steering committee {5d}

Coordinating center and steering committee:Enrolls pediatric practices in the studySupports pediatric practices in recruiting families (if needed) and providing information on the studyAdministrates lists with study center aliases and demographic information of participating practicesGenerates lists for pediatric practices for the allocation of participating families to study aliasesReceives questionnaire results of participating families in the admin area of the e-health online platformProvides the insurance company AOK Baden-Wuerttemberg with the identifiers of participating practices to enable payment for the face-to-face trainingsProvides the insurance company AOK Baden-Wuerttemberg with insurance membership numbers of the participating families for the pre-defined medical data from the families’ health insurance records.

#### Composition of the data monitoring committee, its role, and reporting structure {21a}

A data monitoring committee with a semiannual reporting structure via videoconference is implemented. The data monitoring committee is independent from the sponsor and competing interests.

#### Adverse event reporting and harms {22}

Participating practices and participating families can both report the occurrence of (severe) adverse events to the coordinating center through a study hotline or study email address. The study team manages reported (severe) adverse events.

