#### Intervention description {11a}

Families in the control group receive a face-to-face one-time structured counseling (approximately 30 min) concerning topics shown to have an essential impact on healthy weight development. Similar to the STARKIDS program, the control counselling is provided by medical assistants in participating pediatric practices and addresses the topics healthy weight development, diet, physical activity, media consumption, sleeping habits, and stress. In contrast to the STARKIDS program, the control counselling is limited to providing guideline-based recommendations for each of the covered topics and does not provide further tools such as educative texts, serious games and reflection tools. Families in the control condition receive a flyer summarizing the guideline-based recommendations for a healthy weight development at the end of their one-time structured counseling.

Families in the intervention group receive the newly developed STARKIDS program. The STARKIDS program consists of two steps. The first step consists of face-to-face trainings in the pediatric practice and an e-health online platform. Both include the following modules: “STARKIDS Start,” “eating and drinking,” “activity and media,” “family life,” “STARKIDS Keep on,” and the optional “STARKIDS Joker.” For more details on the individual modules, see Table 1. Every 3 months, families undergo a 90-min-long face-to-face training each covering one module (in the given order) in their pediatric practice, thus continuing for 1 year from first to last face-to-face training. All trainings are taught by a medical assistant and are conducted in the spirit of motivational interviewing [19]. Motivational interviewing is a person-centered counseling style aimed at reducing ambivalence and strengthening internal motivation and commitment to change. The “STARKIDS Joker” is an optional sixth face-to-face training that can be activated by the medical assistant or participating families in case of motivational problems or other issues a family may encounter when implementing the program into their everyday life. This training can be held at any time in between the first and the last training (STARKIDS Start and STARKIDS Keep on).

**Table 1 Tab1:** Overview of the thematic modules in the STARKIDS intervention

Overview	Concept(s)	Educative/interactive texts	Animated films	Reflection tools	Serious games

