**Eating and drinking**					
Information about the dietary concept in STARKIDS	- Why strict diets do not work - What is different in STARKIDS	X	X		
Meal frequency and timing	- Information on meal frequency and timing - Frequently asked questions on this topic	X	X	X	
Drinks	- Drinks, with emphasis on sweet beverages - Frequently asked questions on the topic	X	X	X	X
Primary focus: energy density	- Explanation of the dietary energy density concept - Practical use of the dietary energy concept in daily life - How to make clever food choices based on the dietary energy density concept - Frequently asked questions on the topic	X	X	X	X
Portion sizes	- Information about adequate portion sizes - Examples and tips for choosing adequate meals and snacks	X			
Tips for everyday life	- Tips for grocery shopping - Frequently asked questions about everyday meals - Information about the Nutri-Score	X	X		
Uncontrolled eating	- Information about binge eating, emotional eating, night eating, and grazing - Strategies for avoiding uncontrolled eating - Information for further help in case of eating disorder pathology	X			
Mindful eating and drinking	- Information about how mindfulness can support healthy saturation and indulgence	X			X

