**STARKIDS Joker**					
Strengthening motivation and commitment	- Reflecting individual obstacles and reasons for staying with the program - Developing strategies to strengthen commitment - Tips for introducing change one step at a time	X		X	X

Face-to-face trainings follow a pre-defined sequence containing:Tablet-based pre-assessment: families indicate their previous behavior on the topic of the module, identify problem areas in this topic and rate their current motivational stageDiscussing progress concerning goals and weight trend, problems, and obstacles since the last face-to-face trainingEducational input by the medical assistant about the topics of the current module under consideration of the results of families’ pre-assessmentsChoosing three individual module-specific goals and a weight goal for the next 3 months

The e-health online platform covers different resources allocated to the six modules. Families can watch educative movies, read and interact with educative texts, play serious games, use reflection tools, and utilize so-called tips paper as helpful reminders for changes in everyday life. They are asked to engage with content and different tasks of the respective module and are biweekly reminded to monitor their current goals and the current weight of the child/adolescent.

Step 1 of the STARKIDS program lasts 1 year. To evaluate step 1 of the STARKIDS program and to decide if participants should make use of step 2, pre-defined criteria of BMI reduction is applied_._ Children and adolescents that did not reduce their BMI by the predefined amount receive counselling about further programs and opportunities nearby, depending on the area families are still struggling with. The counselling is given by participating public health services in step 2 (1–2 counselling sessions in a 6-month time frame). Additionally, all families can carry on using the STARKIDS online platform for the next six months after which the program is concluded.

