#### Secondary outcomes

Secondary outcomes originate from a questionnaire which are answered at the three main measurement points and most commonly analyzed as change from baseline. Most variables are assessed twice: once in the parent perspective and once as an own perspective by children aged twelve and older. The secondary outcomes are structured around the main modules of the STARKIDS program. Table 2 contains a detailed overview of outcomes according to intervention modules including their psychometric properties. In summary, the following topics are covered:“Eating and drinking”: dietary intake, rhythm of dietary intake, eating behavior, and knowledge about diet.“Activity and media”: mount and style of physical activity, reasons/aims, and barriers for/to physical activity and support in physical activity. In the field of media consumption, parental mediation, attitudes towards advertising, parent-child conflict and the duration of media consumption are measured and analyzed.“Family life”: psychological variables of interest are disruptive behaviors in children and adolescents, family climate, shared activities, sleep, eating disorder symptoms, body dissatisfaction, stress, and family coherence.

**Table 2 Tab2:** Overview of the questionnaire instruments according to the thematic modules of the STARKIDS intervention

Questionnaire	No. of items	Subscales	Reliability	Validity	Completer (about)
*Overall*					
Quality of Life Questionnaire for children (KINDL^R^), with obesity module *Original title: Fragebogen zur Erfassung der gesundheitsbezogenen Lebensqualität bei Kindern und Jugendlichen (KINDL*^*R*^*)* [23, 25–27]	24 plus 16 (obesity module)	Physical well-being, psychological well-being, self-esteem, family, friends, functioning in school/kindergarten	Cronbach’s *a* = .85	Convergent validity: parent report: *r* = .44–.63; child report: *r* = .33–.59 correlation with SDQ	Parent (child) Adolescent (self)
University of Rhode Island Change Assessment (URICA-S) [28]	16	Precontemplation, contemplation, action, maintenance	Cronbach’s *a* = .61–.84	n/a	Adolescent (self)
Parent Perspective University of Rhode Island Change Assessment -Short (PURICA-S) [24]	16	Precontemplation, contemplation, action, maintenance	Cronbach’s *a* = .30–.84	Criteria validity good to very good (exception subscale precontemplation)	Parent (self)
*Eating and drinking module*					

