### Data collection and management

#### Plans for assessment and collection of outcomes {18a}

Outcomes are assessed at the three measurement time points and collected web-based through the STARKIDS e-health online platform which prevents duplicate measurements. Table 2 shows the applied questionnaires according to intervention modules. Further measurements (e.g., height, weight, somatic comorbidities, and blood levels) are assessed in the pediatric practices at the three measurement time points. The primary outcome BMI-SDS_LMS_ is calculated using the children’s height, weight (both measured in the pediatric practices), age, and gender.

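### The only stated adverse-event route is voluntary reporting by hotline or email, in an unblinded trial with very unequal contact, so adverse-event counts may not be comparable between arms

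*Protocol article*

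**What the plan says.** **Adverse events.** Under Adverse event reporting and harms {22}, practices and families "can both report the occurrence of (severe) adverse events to the coordinating center through a study hotline or study email address". The item ends: "The study team manages reported (severe) adverse events". The article names no other adverse-event route.

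**Contact.** Intervention description {11a} says of the intervention arm: "Every 3 months, families undergo a 90-min-long face-to-face training each covering one module (in the given order) in their pediatric practice". There are five core modules and an optional sixth session. On the platform, these families are also "biweekly reminded to monitor their current goals and the current weight of the child/adolescent". The control arm has a single counselling session of about 30 minutes and a flyer.

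**Blinding.** Who will be blinded {17a} states that practices cannot be blinded. Practices are also among the reporters.

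**Data collected in both arms.** Plans for assessment and collection of outcomes {18a}: "Further measurements (e.g., height, weight, somatic comorbidities, and blood levels) are assessed in the pediatric practices at the three measurement time points". Secondary outcomes, answered by questionnaire at the same three points, include "eating disorder symptoms, body dissatisfaction, stress, and family coherence". Table 2 gives the eating-disorder symptom scale (ChEDEQ-8) and the child body-dissatisfaction scale (IEG-K) to adolescents. The eating-behaviour scale (DEBQ-C: restraint, emotional and external eating) goes to adolescents and to parents reporting on the child. Self-report starts at age 12; enrolment starts at age 3.

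**The concern.** Voluntary reporting finds an event only if someone thinks to report it. Here the opportunity and the prompt to do so differ by arm by design, and half of the reporting chain, the practice, knows the allocation. With equal true risk, the arm seen more often can show more events. Conversely, a real difference can be hidden if the less-seen arm under-reports, and a low count in either arm says little.

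This matters because the programme targets weight in children from age 3 and itself foresees a relevant harm: Table 1 includes "Information for further help in case of eating disorder pathology". The section on discontinuing the intervention also mentions mental illness arising during the trial. A data monitoring committee reports semiannually. Any adverse-event counts by arm that it receives through this route would mix occurrence with ascertainment.

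**Working it through.** The article states no adverse-event rate, safety sample size or safety test, so there is no figure of the plan's own to reproduce. Two checks are possible.

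**1. Scheduled counselling time in step 1** (inputs from Intervention description {11a})

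- Intervention: 5 × 90 = 450 min; with the optional session, 6 × 90 = 540 min.
- Control: about 30 min.
- Ratio: 450/30 = 15 to 540/30 = 18.

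This measures counselling minutes, not opportunities to report. It shows that contact is unequal but does not size the bias.

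**2. Illustration of differential reporting at equal true risk**

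Assumptions (not in the article):

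- each post-baseline practice contact gives one chance to report, with the same probability *q* in both arms;
- the intervention arm has *k* = 5 such contacts (months 3, 6, 9, 12, 18);
- the control arm has *k* = 2 (months 12 and 18, the T1 and T2 measurements), its one counselling session being taken as a baseline contact.

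Share of events reported = 1 − (1 − *q*)^*k*.

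| *q* | Intervention (*k* = 5) | Control (*k* = 2) | Apparent ratio |
|---|---|---|---|
| 0.1 | 0.41 | 0.19 | 2.16 |
| 0.2 | 0.672 | 0.36 | 1.87 |
| 0.3 | 0.832 | 0.51 | 1.63 |
| 0.5 | 0.969 | 0.75 | 1.29 |
| 0.8 | 1.0 | 0.96 | 1.04 |

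As *q* approaches 0, the ratio approaches 5/2 = 2.5.

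The formula gives every event all the post-baseline contacts, so it describes events that arise early. If events are spread evenly over 18 months, later events have fewer contacts left. At *q* = 0.1:

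- Intervention: [3 × (0.4095 + 0.3439 + 0.271 + 0.19) + 6 × 0.1]/18 = 4.243/18 = 0.236.
- Control: [12 × 0.19 + 6 × 0.1]/18 = 2.88/18 = 0.16.
- Ratio: 0.236/0.16 = about 1.47.

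The table is therefore the high side with respect to timing. Reports made by families without any practice contact would narrow the gap further. A higher *q* in one arm, for example because unblinded intervention practices are more alert, would move it either way.

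**3. What is measured alike in both arms** (Table 2 and section {18a})

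| Measure | Age 12 and over | Age 3 to 11 |
|---|---|---|
| Eating-disorder symptoms in the child (ChEDEQ-8) | self-report | none |
| Body dissatisfaction of the child (IEG-K) | self-report | none; parent-rated body-image avatars only |
| Restraint, emotional and external eating (DEBQ-C) | self-report and parent | parent |
| Emotional problems (SDQ) | self-report and parent | parent |
| Comorbidities, blood levels | practice | practice |

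The article states no difference between arms in this schedule. It does not connect any of these measures to item {22} or to the data monitoring committee.

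**The case against.** The strongest reply has four parts.

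- **Harm-relevant data are collected on a schedule.** This stands. A reader might infer that harms are captured only by spontaneous report, or that disordered eating would go unseen. The article does not support that. From age 12, eating-disorder symptoms are measured three times, and restraint and emotional eating are measured at all ages. What is left is narrower: no symptom scale about the child at ages 3 to 11, nothing asked between T0, T1 and T2, and no stated link to safety review. Nor does Table 2 say that the parents' own eating-disorder and body-dissatisfaction scales stand in for the younger child's; they are simply measures of the parent.
- **The route is open to everyone.** Families in both arms can use it without visiting the practice, and both arms attend at T0, T1 and T2. This stands too. Counts may fail to be comparable; it does not follow that they will, or that they are proportional to contact.
- **No between-arm adverse-event test is stated, and the committee's safety content is not described.** Correct. The article therefore does not show that the committee would lack comparable data. The point bears on any comparison that is made, formal or not. The planned models with a group term will estimate differences on the questionnaire scales whatever those scales are called, so relabelling them as harm outcomes would in itself add little.
- **The article condenses a full protocol.** Definitions, forms and review rules may be there, and their absence is not at issue. But item {22} does more than omit: it states a passive method, and that stated choice fits this design poorly.

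**Conclusion.** The point holds in limited form. The stated adverse-event route is voluntary, reporting practices are unblinded, and scheduled counselling differs 15- to 18-fold, so adverse-event counts may not be comparable between arms. The documents do not fix the size. Under the assumed model of 5 against 2 contacts with a per-contact reporting probability of 0.1 to 0.8, equal true risk gives an apparent ratio from about 2.2 down to 1.04, and less if events are spread over follow-up. A roughly twofold artefact cannot be excluded; nor can a negligible one.

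The primary analyses are unaffected. If the full protocol already contains a solicited, arm-identical enquiry, the point is met by saying so in item {22}.

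**What to change.** 1. Add one short adverse-event question set, worded identically in both arms, to the existing T1 and T2 forms: new illness, injury, hospital stay, new mental-health or eating problem since the previous measurement point.
2. Base any between-arm adverse-event comparison on those answers.
3. Keep the hotline and email route, and report what it yields separately as spontaneous events.
4. Include the existing ChEDEQ-8, DEBQ-C restraint and body-dissatisfaction scores by arm in the table for the data monitoring committee. State that, at ages 3 to 11, only parent-reported measures such as DEBQ-C are available.

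The cost is a few items on forms already administered and one table. The forms become slightly longer and more events will be reported. Recall spans 12 months at T1 and 6 months at T2, so minor events will be under-reported, but on the same recall schedule in both arms. The question set equalises the asking; it does not remove the effect of unblinded respondents.

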#### Frequency and plans for auditing trial conduct {23}

Data monitoring will be conducted according to the Center of Clinical Trials (ZKS Tuebingen) internal Standard Operating Procedures (SOPs) and a dedicated monitoring manual for the study. The monitors will review the source documents as needed, to determine whether the data reported in the e-health online platform are complete and accurate. Forty planned monitoring visits are split between high recruiting pediatric practices and randomly selected pediatric practices. The trial steering committee meets at least monthly during the trial period and the data monitoring committee meets semiannual to review conduct throughout the trial period.

#### Plans for communicating important protocol amendments to relevant parties (e.g., trial participants, ethical committees) {25}

All important protocol amendments will be communicated to relevant parties (e.g., participating pediatric practices, ethics committee) through the coordinating center via newsletters or direct contact.

#### Dissemination plans {31a}

Trial results will be communicated by the funder, the participating healthcare insurance company AOK Baden-Wuerttemberg as well as the study team to the public and healthcare professionals through websites, newsletter, and publications.

## Discussion

The stepwise, combined face-to-face, and e-health-supported STARKIDS program is a low-threshold intervention program for families with children/adolescents with overweight or obesity. The program has several advantages: (1) the stepped procedure and the accompanying e-health aspects enable adaptions of the program to the individual families (e.g., concerning frequency and duration as well as focal points with regards to content), (2) the program is designed for the whole family and takes parents perspectives as well as adolescents perspectives into account, (3) face-to-face trainings in families local pediatric practices with their known healthcare providers facilitates access to the program and promotes adherence.

Potential issues in performing the study might arise from placing the face-to-face trainings in the pediatric practices, especially in light of the high burdens of pediatricians in the ongoing COVID-19 pandemic. They are however parents preferred professionals for broaching the topic of their children’s/adolescents’ weight and giving guidance [68]. Furthermore, face-to-face trainings are conducted by medical assistants in the pediatric practices, strengthening and expanding their roles in respective practices. Additionally, through the combination of face-to-face trainings and e-health components of the STARKIDS intervention, the program provides a timely presentation of prevention and intervention materials. Evidence for adolescents also suggests that especially health education, goal setting, and self-monitoring can be effectively delivered via websites [69]. In light of the ongoing COVID-19 pandemic in which obesity in children and adolescents has become an even more urgent health problem [70, 71], we therefore hope to support children/adolescents with overweight/obesity and their families in a healthy weight development.

